## 1.2 Final protocol (link to publication)

Our final protocol is published open access in the following manuscript (digital object identifier: [10.3390/healthcare6030085](https://doi.org/10.3390/healthcare6030085)).

[name], [name], [name], [name], [name], [name], [name], [name], [name], [name], [name], [name], [name]. Rationale and protocol for a randomised controlled trial comparing fast versus slow weight loss in postmenopausal women with obesity – the TEMPO Diet Trial. Healthcare (Basel) 2018;6.

### 1.3 Summary of changes from original protocol

#### 1.3.1 Changes made before recruitment of first participant

The first participant was recruited into the TEMPO Diet Trial on 24 March 2014, as listed on the Australian New Zealand Clinical Trials Registry (Number 12612000651886). As such, all of the following changes (made on 29 November 2013) occurred before recruitment of the first participant.

- Title was changed to The TEMPO Diet Trial: Type of Energy Manipulation for Promoting optimum metabolic health and body composition in Obesity. This title was developed as part of our recruitment strategy.
- Using the very low energy diet (VLED) for a period of 4 months, instead of a minimum of 3 months and a maximum of 5 months. This change was made to reduce variability in the results. Patients at the Metabolism & Obesity Services at Royal Prince Alfred Hospital routinely use VLEDs for periods of 4 months.
- Three additional inclusion criteria and a screening step were added. For safety, participants must not have any contraindications for following a VLED, and they must not have donated whole blood in the 3 months preceding the trial. As this trial is labour intensive for both investigators and participants, we also needed to ensure that potential participants would be capable of completing activities required for this trial, such as keeping food, activity and sleep diaries at home, wearing accelerometers and temperature trackers for 7 days at a time, and keeping appointments with our team. Thus, after signing the consent form, potential participants would be required to complete these screening activities prior to being randomised for the trial.
- One exclusion criterion was slightly modified. Instead of ‘no metal in the body’, this was changed to ‘no loose metal in the body’. Unlike loose metal such as pacemakers or bullets, metal that is fixed, such as titanium fastened to bones in joint replacements, is not a contraindication for the magnetic resonance imaging and magnetic resonance spectroscopy to be used in this trial.
- The provider of the VLED meal replacement formula was changed from Nestlé (Optifast®) to Prima Health Solutions (KicStart™). Both Optifast® and KicStart™ VLEDs are routinely used in the Metabolism & Obesity Services at Royal Prince Alfred Hospital, because an independent study has shown both to be the most nutritionally complete VLED products available. Prima Health Solutions was able to offer their product, KicStart™, at a lower cost than Nestlé.
- Fasting urinary and whole blood ketone concentrations would be measured, instead of fasting serum ketone levels as in the original protocol, because measurements of ketones in urine and whole blood are more common than serum measurements.

- The protocol for the appetite test was changed to reflect current literature. Instead of consuming one meal replacement formula as a liquid meal, participants would consume a meal that more closely resembled a normal breakfast (toast, margarine, eggs, orange juice). This was necessary to more accurately assess changes in appetite over the course of the trial. In addition, 2 mL of blood would be taken from a venous cannula at 7 time points during the appetite test. These samples would be used to assess plasma concentrations of gut-derived appetite-regulating hormones, notably ghrelin, peptide YY and leptin, in order to provide greater depth of understanding of any associated changes in appetite.
- Pedometers would be used to assess activity, in addition to the accelerometers approved for use in the original protocol. The pedometer would be given to each participant to keep, to help promote regular and ongoing physical activity.
- Body temperature would be assessed by continuously measuring peripheral skin temperature on the upper arm for up to 7 days at a time.
- The list of bone turnover markers to be measured was refined. This change would enable the most cost-effective analysis of bone turnover markers.
- The list of questionnaires to be used in this trial was expanded. This change was implemented following discussion with our collaborators, with the aim of maximising information obtained from this trial. It would enable us to determine whether fast versus slow weight loss has differential effects on eating behaviours such as bingeing or purging, as well as general mental health, mindfulness and personality.
- Vascular function and structure tests were modified to reduce costs (including staffing costs) and participant burden. Glyceryl trinitrate (GTN) would no longer be used during measurement of flow-mediated dilatation (FMD). EndoPAT or pulse wave velocity tests of vascular health would no longer be used.
- One additional dual energy X-ray absorptiometry (DXA) scan was added to the protocol. Its purpose was to check for osteoporosis, an exclusion criterion for our trial. It would occur during screening, for participants who have not had a clinical DXA scan to assess bone density within the past 2 years, or for participants who have had such a scan within the past 2 years but whose result was close to the definition of osteoporosis. This additional DXA scan would not be used for data analysis.
- Sympathetic reactivity (using doppler fluximetry) was not included in the final protocol, as we did not have access to equipment to measure this.
- The 6-minute walking test was removed from the final protocol, as we did not have access to a non-slip under-cover venue in which to conduct this test uniformly in varying weather conditions.

### 1.3.2 Changes made after recruitment of first participant

With the first participant being recruited on 24 March 2014 (Australian New Zealand Clinical Trials Registry Number 12612000651886), the following change (implemented on 9 July 2014) was made after baseline testing of the first 13 participants.

- The Loss of Control Over Eating Scale (LOCES) was added after discussion and agreement with collaborators that this measure would provide additional insights into eating behaviour (including eating disorder behaviours) that was not available from the other questionnaires being used in the trial.

## 2 Statistical analysis plan

### 2.1 Original statistical analysis plan

Our original statistical analysis plan is in our original protocol, under the headings of “Database maintenance and data analysis” and “Data Analysis”.

### 2.2 Final statistical analysis plan

A summary of our final statistical analysis plan is included in the current manuscript, under the heading of “Statistical Analysis”. A detailed version of this is below.

For our primary outcome of whole-body lean mass at 12 months after intervention commencement, we calculated that a target sample size of 100 participants would provide a power of 90% at a two-sided alpha level of 5%, allowing for up to 20% attrition as seen in previously-published weight loss interventions. Notably, attrition at 12 months in our current trial was 16% (to be detailed in the Results section), which fell within the attrition prediction used in our sample size calculation. Specifically, to detect a 5% difference in whole-body lean mass (e.g. 50.3 kg versus 53.0 kg, and assuming a variance of 5 kg), the effect size is 0.52, so at 90% power and  $P < 0.05$ , a sample size of 39 participants per group would be necessary, therefore with 20% attrition we would need 50 participants in each group. Further, based on studies in participants with obesity that elicited comparable weight losses to that anticipated from the SEVERE intervention in this trial, i.e. 12-20% of initial body weight over 12 months, the effect size to detect differences between interventions in the change in bone mineral density are large ( $> 0.8$ ), indicating that a sample of 20 per group would provide 90% power to detect significant ( $P < 0.05$ ) differences between interventions.

Statistical analyses were performed using SPSS Statistics Version 24 for Windows (IBM Corporation, New York, NY, USA). Statistical significance was accepted as  $P < 0.05$ . Fisher's exact tests were used to compare categorical demographic characteristics (age, ethnicity) and attrition between groups (i.e. SEVERE versus MODERATE). To compare continuous variables between groups at baseline (0 months), Mann-Whitney tests were used. All continuous variables were assessed for normality before analysis using histograms and P-P-plots. Where data were not normally distributed, a natural log-transformation was applied to obtain a normal distribution, although means and confidence intervals are reported on untransformed data.

To compare longitudinal changes between groups, intention-to-treat analysis was performed using data from all participants originally randomized, using random effects linear mixed models. Mixed model analyses were used instead of standard repeated measures analysis of variance because of the likelihood that there would be dropouts and missed visits that preclude the use of the classical approach. Therefore, this model allowed for participants to have partial missing data and still be included without imputation. Intervention group and time (0, 4, 6, and 12 months for all parameters except for waist circumference, hip circumferences, and waist to hip ratio, which were assessed at all of these points plus at 0.25 and 1 months), were included as fixed effects, and participant was included as a random effect and included an intercept. Nominal

time was used, although measurements at 0 and 0.25 months were always done exactly 1 week apart, measurements at 1 month were done within  $\pm 2$  days from the exact date, measurements at 4 and 6 months were done within  $\pm 1$  week from the exact date, and measurements at 12 months were done within  $\pm 2$  weeks from the exact date. For all outcomes, baseline values of the relevant variable were added as a covariate in the analysis because when, by chance, there happens to be imbalance in the baseline covariate between groups, even when the two treatment groups are well balanced, adjusting for the covariates will (for linear models) give a more precise estimate of the treatment effect.

As the degree of physical activity is known to influence measures of body composition, physical activity (expressed in metabolic equivalents of task, or METs) was added as a covariate, as measured at each of the timepoints. Maximum-likelihood estimation was used, and an unstructured covariance matrix was specified to account for the correlation between repeated measures over time by allowing the intercept for individuals to vary randomly. When the overall P value for the interaction between group and time was less than 0.05, Bonferroni adjustments were used to correct for multiple comparisons between groups at each time point. As a secondary analysis, the model was further adjusted for weight at each time point, because lighter individuals are known to have lower whole-body lean mass and BMD than heavier individuals. This was to determine if there was an effect of the interventions beyond that which would be expected due to weight loss.

Within-group changes were analysed with repeated measures linear mixed models. Intervention group and time were included in the model as fixed effects, and time as a repeated measure, with physical activity (METs) added as a covariate. Maximum-likelihood estimation was used, and an unstructured covariance matrix was specified. When the overall P value for the interaction between group and time was less than 0.05, Bonferroni adjustments were used to correct for multiple comparisons between time points and baseline (0 months) within each group.

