**Sample size.** Our sample size of 100 women (50 on each diet) was selected based on the following power calculations and allowing for up to 20% attrition as we have seen in our previously published weight loss interventions. Most stringently, even if there is only a 5% difference between groups in – for example – fat free mass at any time point, we have the statistical power to detect it. Indeed, to detect a 5% difference in fat free mass (e.g. 50.3 versus 53.0 kg, and assuming a variance of 5 kg), the effect size is 0.52, so at 90% power and  $P < 0.05$ , it is necessary to study 39 women per group (50 – 50 x 20% attrition = 40). For other parameters under study, the samples sizes required to detect clinically meaningful differences between diets are smaller. For instance, based on studies in obese subjects that elicited a comparable weight loss to the 12-20% over 12 months that is expected in the current work, the effect size to detect differences between diets in the change in circulating thyroid hormone concentrations, bone mineral density and thigh muscle diameter are large ( $> 0.8$ ), indicating that a sample of 20 per group would provide 90% power to detect significant ( $P < 0.05$ ) differences between diets. From

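### The primary sample-size statement is out by a factor of two: 39 per group gives about 62% power for effect size 0.52 in the unadjusted comparison described, not 90%

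*Supplement*

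**What the plan says.** The sample-size paragraph of section 2.2 opens with "For our primary outcome of whole-body lean mass at 12 months after intervention commencement" and claims 90% power at a two-sided 5% level with 100 participants, allowing for 20% attrition. The target is a 5% difference between the groups, illustrated as "e.g. 50.3 kg versus 53.0 kg, and assuming a variance of 5 kg". It continues "the effect size is 0.52, so at 90% power" and concludes that "a sample size of 39 participants per group would be necessary, therefore with 20% attrition we would need 50 participants in each group". It adds that observed attrition at 12 months was 16%, within the allowance.

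The same calculation stands in section 1.1 (Original protocol, Sample size), there for fat free mass: "it is necessary to study 39 women per group". It was carried into the final plan with its figures unchanged.

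Neither version of the calculation mentions a paired design, a one-sided test, a baseline correlation or any other reduction in variance. The analysis model, described later in section 2.2, is a linear mixed model with the baseline value of the outcome as a covariate.

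**The concern.** An effect size of about 0.5 with 90% power usually calls for some 80 participants per group in a parallel two-arm trial, so 39 looks like half the right answer. The inputs also sit awkwardly together. The plan writes "assuming a variance of 5 kg), the effect size is 0.52", but a variance is not measured in kg, and 2.7 kg divided by 5 kg is 0.54.

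The trial asks whether severe energy restriction costs more lean mass than moderate restriction. A reader who accepts 90% power for a 5% difference may take a non-significant result as evidence that no such loss occurs. In the calculation as stated, a true difference of that size would be missed in 35% to 38% of trials (42 or 39 completers per group).

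**Working it through.** **Inputs, all from section 2.2:** two parallel groups; d = 0.52; two-sided alpha 5% (z = 1.96); power 90% (z = 1.2816); means 50.3 and 53.0 kg; spread 5 kg; 39 per group before and 50 after the attrition allowance; observed attrition 16%.

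**1. Where 39 comes from.** The one-sample (or paired) formula gives

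n = (1.96 + 1.2816)² / 0.52² = 10.508 / 0.2704 = 38.9, rounded up to 39.

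**2. Two independent groups.** The variance of a difference between two means carries a factor of 2:

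n per group = 2 × 10.508 / 0.2704 = 77.7, rounded up to 78.

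The noncentral t gives 78.7, rounded up to 79. The stated 39 would also arise if 78 per group had been read as a total. The documents do not show which slip occurred.

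**3. Power at the numbers available (two-sample t-test, two-sided 5%).**

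| n per group | d = 0.52 | d = 0.54 |
|---|---|---|
| 39 (as stated) | 62.1% | 65.3% |
| 40 (50 less 20%) | 63.2% | 66.5% |
| 42 (50 less 16%, assumed equal by arm) | 65.4% | 68.6% |
| 50 (no attrition) | 73.1% | 76.2% |
| needed for 90% | 79 | 74 |

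A normal approximation gives 63.2% in place of 62.1% for 39 per group at d = 0.52.

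**4. Other unadjusted two-sample readings (normal approximation, n per group).**

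- One-sided, 90% power, d = 0.52: 64
- Two-sided, 80% power, d = 0.52: 59
- One-sided, 80% power, d = 0.52: 46
- Variance of 5 taken literally, so SD = √5 = 2.24 and d = 2.7/2.24 = 1.21: 15

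None gives 39. The last also shows that 5 must be meant as an SD, since only then is the effect size near 0.52.

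**5. Effect size.** (53.0 − 50.3)/5 = 0.54. An SD of 5.2, rounded to 5 in the text, would give 2.7/5.2 = 0.52.

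**6. Difference detectable with 90% power, SD 5 kg.** With 40 per group, d = 0.734, so 0.734 × 5 = 3.67 kg, about 7% of 50.3 to 53.0 kg. With 42 per group, d = 0.716, so 3.58 kg.

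**7. Attrition step.** 39/0.8 = 48.75, so 49, rounded to 50: sound in itself. Applied to 79 it gives 79/0.8 = 98.75, so 99 per group and 198 in total, against 50 and 100.

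**8. Effect of baseline adjustment.** With a correlation r between baseline and 12-month lean mass, the variance falls by the factor 1 − r². Normal approximation, d = 0.52; the values of r are assumptions, as the documents give none:

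| r | n per group for 90% | power at 39 |
|---|---|---|
| 0 | 78 | 63.2% |
| 0.5 | 59 | 75.5% |
| 0.6 | 50 | 81.9% |
| 0.7 | 40 | 89.5% |
| 0.8 | 28 | 96.9% |
| 0.9 | 15 | over 99% |

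Using the t-based detectable effect, 40 per group reaches 90% when r ≥ √(1 − (0.52/0.734)²) = 0.71, or √(1 − (0.54/0.734)²) = 0.68 for d = 0.54.

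**The case against.** The strongest reply is that 62% belongs to an analysis the plan does not use. The mixed model adjusts for baseline, lean mass in the same woman may correlate strongly over a year, and at r = 0.8 the power with 39 per group is about 97%. This stands as a limit on the conclusion: it does not follow that the trial's real power was 62%. It does not rescue the statement. The paragraph derives 39 from an unadjusted standardised difference, makes no appeal to adjustment and gives no correlation. The plan also applies a Bonferroni correction to the between-group comparisons at each time point after the interaction test, which the sample-size calculation ignores and which lowers power.

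Two smaller objections stand in part. The gap between 0.52 and 0.54 may be only rounding of the SD, so it is a query for the authors and not a proven error. The 42 per group assumes 50 randomised to each arm and equal attrition, since section 2.2 gives only the overall 16%.

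It can also be said that the trial is already run, so nothing but wording changes. That is true of the cost, but the 90% figure is still how readers will judge a null primary result.

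**Conclusion.** The point holds. On the plan's own inputs, and for the unadjusted two-group comparison it describes, 79 women per group are needed for 90% power, not 39, and 39 to 42 per group give 62% to 65%. Using d = 0.54 instead raises this to 65% to 69% and leaves the conclusion unchanged. The result assumes that 5 kg is an SD and that the groups are of equal size. The power of the baseline-adjusted analysis cannot be determined from the documents: it is at least 90% if the correlation is about 0.7 or higher, before any multiplicity correction, and lower otherwise. Because the error is in the stated power for the primary outcome, it must be corrected.

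**What to change.** Reword the sample-size paragraph of section 2.2; no further enrolment or change of analysis is needed.

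- State that 39 to 42 completers per group give about 62% to 65% power for an effect size of 0.52 in an unadjusted comparison, or 90% power for a difference of about 3.6 to 3.7 kg with an SD of 5 kg (40 to 42 per group).
- If 90% power for a 5% difference is to be claimed, base it on the baseline-adjusted analysis. State the correlation required (about 0.7 or more), give its source, and say how the Bonferroni step was treated.
- Write SD in place of variance. Reconcile the effect size with the example: give the unrounded SD if it was about 5.2 kg, otherwise use 0.54 or change the example means.
- Interpret a non-significant primary result from its confidence interval, in particular whether it excludes a 5% difference, and not from the planned power.

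The cost is a rewritten paragraph and a less favourable power statement, unless a correlation can be documented.

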## RESEARCH PLAN AND METHODOLOGY

**Participants.** This study will be performed in women because the estimated lifetime risk of osteoporotic fractures is 3-fold higher in women than in men (40% versus 13%). Additionally, while the prevalence of obesity is similar in both sexes, over 70% of the people presenting for treatment at the Metabolism & Obesity Services (Royal Prince Alfred Hospital) are women. One hundred (100) 45-65 year old women will be recruited, all of them sedentary (< 60 minutes physical activity / week) with class I or II obesity (30-40 kg.m^2). All women will be at least 5 years post-menopausal, to circumvent known effects of female sex hormone cycles and the menopausal transition on parameters under investigation. Eligibility for the study requires subjects to be euthyroid, non-diabetic, non-osteoporotic, non-smoking, ambulatory, weight stable for at least 6 months ( $\pm$  2 kg) and not taking medications known to affect heart rate, body composition or bone mass (e.g. glucocorticoids or beta blockers), no anti-resorptive therapy within the last 3 years, and no alcohol or drug dependency. Participants must not have metal in the body (e.g. from a pacemaker), as this is contraindicated for magnetic resonance imaging and

magnetic resonance spectroscopy. Respondents will be interviewed by telephone and if classified as eligible based on height, weight and medical history, will be invited to attend an information session.

**Participants will be randomised to VLED or conventional diet.** Both interventions will be administered at the Metabolism & Obesity Services and overseen by [name] and [name] and [name]. By having the interventions administered by actual clinical services rather than by our research laboratory, our findings will reflect effects of each diet as administered in the real world. We already know that both VLED and conventional diet result in average weight losses of approximately 20% and 12% of initial body weight after 12 months, respectively, and this study will demonstrate the effects of such real world clinical interventions on important parameters of long-term health and wellbeing, notably body composition and the factors that influence it.

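### The final SAP's claim that 20 women per group give 90% power for bone mineral density does not follow from an effect size stated only as above 0.8; at 0.8 the power is 69% and 34 per group are needed

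*Supplement*

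**What the plan says.** The sample-size paragraph of section 2.2 (Final statistical analysis plan) makes two power statements.

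- **Primary outcome.** For whole-body lean mass at 12 months, the target of 100 women "would provide a power of 90% at a two-sided alpha level of 5" per cent. The plan gives an effect size of 0.52 and a requirement of 39 per group, and adds: "therefore with 20% attrition we would need 50 participants in each group".
- **Bone mineral density.** Drawing on studies of comparable weight loss, the plan puts the effect size separating the two diets at above 0.8, and describes it as large. From that bound alone it reaches its statement on sample size: "indicating that a sample of 20 per group would provide 90% power to detect significant" effects. No point value, mean difference or standard deviation is given for bone mineral density.

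The significance level is given once for all analyses: "Statistical significance was accepted as $P < 0.05". The attrition allowance is also given once: "allowing for up to 20% attrition as seen in previously-published weight loss interventions".

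**The concern.** The only effect-size figure offered for bone is the bound of 0.8, and the sample of 20 per group is presented as its consequence. A power statement that rests on an effect being above some value should hold at that value. This one does not: for a between-group test it fails from 0.8 up to about 1.05.

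Bone mineral density is the only outcome besides the primary for which the final plan states power, and loss of bone is one of the harms the trial was set up to examine. Someone reading a non-significant bone result beside this sentence would believe that the comparison had twice the women it needed (20 required, 40 expected after attrition). That would encourage reading the null result as stronger reassurance than the design gives.

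**Working it through.** **Inputs, all from section 2.2**

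- Standardised difference d: above 0.8, tested at the bound, d = 0.8.
- Stated n: 20 per group, two groups of equal size.
- Stated power: 90%.
- Alpha: 0.05. The bone sentence does not repeat the sidedness; two-sided is assumed, as for the primary outcome.
- Planned size: 50 per group. After 20% attrition, 50 × 0.8 = 40 per group.

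**Step 1. Try to reproduce the plan's figure (d = 0.8, 20 per group, 90%).**

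Normal approximation: power = Φ(d·√(n/2) − 1.96) = Φ(0.8 × √10 − 1.96) = Φ(2.530 − 1.960) = Φ(0.570) = 71.6%.

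Noncentral t with 38 degrees of freedom: 69.3%.

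Other variants at d = 0.8 with 20 per group:

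| Variant | Power |
|---|---|
| Two-sided, t | 69.3% |
| Two-sided, normal | 71.6% |
| One-sided, t | 79.9% |
| One-sided, normal | 81.2% |
| Baseline-adjusted, correlation 0.5 (normal) | 83.2% |
| Baseline-adjusted, correlation 0.6 (normal) | 88.5% |
| Baseline-adjusted, correlation 0.65 (normal) | 91.5% |

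No unadjusted two-group calculation gives 90%. Baseline adjustment gets there only with a correlation between about 0.6 and 0.65, and the plan states none.

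**Step 2. Sample size for 90% power at d = 0.8.**

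n per group = 2(1.960 + 1.282)²/d² = 2 × 10.507/0.64 = 32.8, so 33. With the t distribution it is 33.8, so 34 per group.

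**Step 3. Effect at which 20 per group do give 90%.**

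d = 3.2415 × √(2/20) = 1.03 (normal); 1.05 (t). Power at 20 per group between the bound and that value (t):

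| d | Power with 20 per group |
|---|---|
| 0.80 | 69.3% |
| 0.90 | 79.2% |
| 1.00 | 86.9% |
| 1.05 | 89.9% |
| 1.10 | 92.4% |

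**Step 4. What the planned trial provides (t, single two-sided 5% test).**

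- 40 per group at d = 0.8: 94.2%.
- 50 per group at d = 0.8: 97.7%.
- Effect detectable with 90% power at 40 per group: 0.73 (the normal approximation gives 3.2415 × √(2/40) = 0.72).

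**The case against.** The best defence is that the plan says above 0.8, not equal to 0.8. If the cited studies pointed to 1.05 or more, 20 per group would be right. This stands to a point: it rules out calling the figure wrong outright, because the effect size actually used is not disclosed. It does not rescue the sentence, because nothing in the plan lets a reader confirm a value that large, and the inference as written runs from the bound.

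A one-group calculation may lie behind the figure. A one-sample or paired t test at d = 0.8 needs 18.4, so 19, close to 20. The neighbouring lean-mass figure also fits a one-sample formula: 10.507/0.52² = 38.9, against 2 × 10.507/0.52² = 77.7, so 78 per group, for two groups. This is suggestive but remains inference, and the lean-mass calculation is a separate matter.

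The second defence is that 20 per group is not a design number. The trial was sized at 50 per group on lean mass, and even the recalculated 34 lies below the 40 expected. This stands fully and limits the consequence.

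Three stronger readings might tempt a reader, and the documents do not support them.

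- **Power falls below 90% once visits are corrected for.** The plan applies Bonferroni only after a significant group-by-time interaction and states no divisor. Single-visit t tests at a divided alpha are therefore not the power of the planned analysis.
- **The 0.8 is really a change within one diet, so the contrast between diets is much smaller.** The plan says explicitly that the effect size is for differences between interventions. The cited studies are not available to test that.
- **The 12–20% weight-loss range is inconsistent.** The plan ties it to the SEVERE arm, while the Participants section of the original protocol gives about 20% and 12% for the two diets. The original protocol has been superseded, and the range does not enter the calculation.

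**Conclusion.** The point holds in limited form. At the stated bound, 20 per group give 69% power, about 21 percentage points below the 90% claimed, and 34 per group are needed. The claim is true only for an effect of about 1.05 or more, which the plan does not state.

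It would be too much to conclude that the bone comparison is underpowered. With 40 per group it has about 94% power at 0.8 for a single two-sided 5% test. What is overstated is the margin: 40 expected is about 1.2 times what is needed (40/34), not twice (40/20).

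These figures assume a two-sided test, equal groups, an unadjusted comparison of two means and planned attrition of 20%. Baseline adjustment or use of repeated measurements could raise power, but the plan gives no correlation from which to credit it.

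**What to change.** Replace the bone sentence in section 2.2. If 0.8 is the intended effect, wording such as this would do:

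> For change in bone mineral density, 34 participants per group are needed for 90% power at a between-intervention effect size of 0.8. The 40 per group expected after 20% attrition give about 94% power at 0.8, and 90% power for an effect of about 0.73 (single two-sided 5% test).

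If a larger effect was used, keep 20 per group but state that effect size (about 1.05), the between-diet difference and standard deviation behind it, and the source.

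The cost is wording only. No participants, visits or analyses change. With the first option the stated requirement becomes less favourable, but the planned sample still meets it.

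### For log-transformed outcomes, the test and the reported confidence interval concern different quantities; this matters for strongly skewed secondary outcomes and hardly for the primary one

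*Supplement*

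**What the plan says.** Section 2.2 of the final SAP sets the rule in two sentences. First, "All continuous variables were assessed for normality before analysis using histograms and P-P-plots". Then, for variables that fail this check, "a natural log-transformation was applied to obtain a normal distribution, although means and confidence intervals are reported on untransformed data".

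The same section goes on to the between-group comparison: "intention-to-treat analysis was performed using data from all participants originally randomized, using random effects linear mixed models", with group and time as fixed effects and the baseline value and physical activity as covariates. Comparisons at single time points are gated: "When the overall P value for the interaction between group and time was less than 0.05, Bonferroni adjustments were used".

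Four things are not stated:
- which outcomes were transformed;
- which scale the model estimates and P values are on when one was;
- whether the untransformed intervals are for group means, for changes or for between-group differences;
- whether any log-scale result is back-transformed. Geometric means and ratios are not mentioned.

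**The concern.** The transformation is made for the analysis, and only means and confidence intervals are exempted from it. The natural reading is therefore that P values come from the log-scale model and intervals from the raw scale.

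These answer different questions. A linear model for ln(Y) compares mean logs, so its exponentiated contrast is a ratio of geometric means. An interval on untransformed data concerns arithmetic means. The two have different point estimates and standard errors, and need not agree about the null.

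What is at stake depends on what the interval is for:
- **Between-group difference.** A reader may meet P < 0.05 beside an interval that includes zero, or the reverse, with no means of telling which to believe.
- **Group means only.** There is no zero to include, so no direct contradiction. But the effect that was tested then has no reported estimate or interval.

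The trigger is also misplaced. The mixed model needs roughly normal residuals and random effects, given group, time and covariates. The SAP inspects the variables themselves before analysis. A pooled histogram can look skewed because visits or groups differ, and can look acceptable when the residuals are not.

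**Working it through.** The documents give no log-scale result to reproduce, so the check is how often test and interval would disagree, as a function of skewness.

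**Inputs**
- Completers per group: the SAP says "attrition at 12 months in our current trial was 16" per cent. With 100 planned and equal attrition assumed, 100 × 0.84 / 2 = 42.
- Spread of lean mass: "e.g. 50.3 kg versus 53.0 kg, and assuming a variance of 5 kg". The unit is kg, so 5 is read as an SD. Mean = (50.3 + 53.0)/2 = 51.65; coefficient of variation = 5/51.65 = 0.097; log-SD = √ln(1 + 0.097²) ≈ 0.10. The SD implied by the stated effect size, 2.7/0.52 = 5.19, gives the same rounded figure. If 5 were truly a variance, the SD would be √5 = 2.24 and the log-SD about 0.04, so conflict would be rarer still.
- Larger log-SDs and all effect sizes below are assumptions; the documents give none.

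**Why the two can differ.** For lognormal data the geometric mean is exp(μ) and the arithmetic mean is exp(μ + σ²/2). The log test concerns μ₁ − μ₀; the raw interval concerns exp(μ₁ + σ₁²/2) − exp(μ₀ + σ₀²/2).

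**Simulation.** 40,000 replicates, 42 per group, one time point, no covariates. A two-sided t-test on logs is set against the 95% interval for the raw mean difference. Each cell is P(log test significant and raw interval includes 0) divided by P(log test significant).

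| Log-SD | Standardised effect 0.3 | 0.5 | 0.63 |
|---|---|---|---|
| 0.10 | 0.0093/0.271 = 3.4% | 0.0117/0.621 = 1.9% | 0.0084/0.813 = 1.0% |
| 0.25 | 0.0241/0.275 = 8.8% | 0.0321/0.621 = 5.2% | 0.0241/0.815 = 3.0% |
| 0.50 | 0.0543/0.275 = 19.7% | 0.0795/0.620 = 12.8% | 0.0662/0.812 = 8.2% |
| 1.0 | 0.1176/0.273 = 43.1% | 0.2084/0.622 = 33.5% | 0.2041/0.814 = 25.1% |

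A repeat run with standardised effect 0.4 at log-SD 0.25 gave 7.0%, so the range there is about 3–7% for effects of 0.4 to 0.63.

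With geometric mean ratios of 0.65 to 0.8 instead, the share is about 8–44% over log-SD 0.6 to 1.0 (27% at log-SD 0.8 and ratio 0.7). Repeat runs move the ends by a point or two. In a further 1–4% of all trials only the raw interval excludes zero.

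**Unequal spread.** Set equal arithmetic means with log-SDs of 0.5 and 0.9. The true geometric mean ratio is exp(−(0.81 − 0.25)/2) = exp(−0.28) = 0.76. Using Welch tests, the log test rejects in 41% of trials and the raw test in 7%. They disagree in 36%, and the two estimates have opposite signs in 43%.

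**Coverage of the raw interval.** At log-SD 0.6 to 1.0 and the same ratios, the 95% interval for the difference in arithmetic means covers 94.6–95.4%. The interval for a single group mean covers about 93% at log-SD 0.6 and 89% at 1.0.

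**After the fix.** Exponentiation is monotone. The interval for the ratio excludes 1 exactly when the log-scale interval excludes 0, that is, when the test is significant under the same adjustment. Disagreement is then 0% by construction.

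**The case against.** The strongest reply is that the outcomes the SAP names are not very skewed: lean mass, bone mineral density, waist and hip circumference and their ratio. The plan's own figures put lean mass at log-SD about 0.10, where conflict is rare. The large percentages need log-SDs that appear nowhere in the documents. Skewed measures such as hepatic fat and hormones are in the protocol, but nothing says that they fall under this SAP or that they were transformed. This stands, and it limits the point to whichever outcomes were both transformed and strongly skewed.

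The illustration also leaves out the planned baseline covariate. In a two-group analysis of covariance with assumed baseline correlations, the share was:
- 0–4% at log-SD 0.10–0.20 (correlation 0.9, ratios 0.90–0.97);
- 0.3–11% at 0.35–0.5 (correlation 0.8, ratios 0.8–0.9);
- 24% at 0.8 (correlation 0.7, ratio 0.7), against 26% unadjusted in the same check.

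So adjustment does not remove the conflict under strong skewness. Nor does it turn a ratio of geometric means into a difference of arithmetic means.

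The text says means, not mean differences. If the raw figures are descriptive group means, the contradiction does not arise as such. That is fair, but the remedy is the same, because the tested effect would then be left without an interval.

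A reader might also infer that the raw interval is invalid because normality had been rejected. The calculations do not bear this out for a mean difference: skewness largely cancels between equal-sized groups, and coverage stays near nominal. Only single-group intervals under-cover. The fault is that the interval belongs to a different quantity from the one tested.

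**Conclusion.** The point holds as a mismatch between what is tested and what is reported, for any outcome analysed on the log scale. It rests on reading the P values as log-scale results, which the SAP implies but does not state word for word.

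Its size depends on skewness. For the primary outcome it is about 1–3% of significant results even if lean mass were transformed, which nothing in the documents says it was. A reader should therefore not infer that the primary conclusion is at risk. The conflict becomes common, in the tens of per cent, only for strongly skewed outcomes, and those figures come from assumed lognormal data in a single-time-point, two-group simplification. It is worth correcting because the rule is invoked precisely when data are skewed and the correction is nearly free.

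**What to change.** For each outcome analysed on the log scale:
- report the exponentiated group contrast as a ratio of geometric means, with the interval from the same model as the P value;
- apply to that interval the same multiplicity adjustment as to the P value. An unadjusted 95% interval beside a Bonferroni-adjusted P value is a separate source of disagreement;
- keep raw means if wanted, labelled as descriptive.

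List the transformed outcomes, and judge the need for transformation from the residuals of the fitted mixed model rather than from the raw distribution of each variable.

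The cost is small. The fitted log models already hold the estimates, so the work is exponentiation, residual plots and new table labels. The one downside is that these outcomes read as percentage differences rather than in their own units.
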